### Adherence to intervention

Training modules for outpatient nurses and doctors are expected to play a fundamental role in improving adherence of medical staff in practices to the intervention protocols. Training will be carried out by the consortium lead, a member of the public health department in Heidenheim as well as the lead of the physician association in Heidenheim. They will be supplemented by monthly case conferences /seminars hosted by the study team of the Heidenheim Clinic as well as personal site visits by the lead study nurse to all practices in order to provide individualized support. Moreover a support system will be established comprising an email service and a study hotline which can be used by both patients and providers. Inpatient processes will be under direct supervision of the internal study team in the Heidenheim clinic.

Patients who can decide to discontinue their participation in the study at any point in time. As compliance is also a relevant endpoint in this study, discontinuation of the decontamination process (i.e. due to related side effects, lack of motivation) without wishing to be excluded from the study itself, will not lead to exclusion from the analysis (primary analysis as intention to treat). Adherence to the intervention will be closely monitored via a decontamination schedule, where patients are required to tick off all completed decontamination steps. Patients may call link nurses in the GP practices for further information. A direct clinical supervision is not possible as the decontamination is self-administered in the home setting.

### Adverse events

All adverse events related to the intervention that lead to a discontinuation of the study will be documented by study personnel in the Heidenheim clinic. Reasons for discontinuation of the decontamination procedure will be collected via patient questionnaires. Adverse events directly related to the intervention (i.e. reaction of the skin, allergic reactions) are, however, expected to be rare.

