### Statistical analysis

**The primary endpoint** (comparison of colonization rates prior to surgery) will be analysed separately for MRSA and MSSA using logistic regression modelling with GEE (Generalized Estimation Equation) correction to account for potential cluster effects. The power calculation (see section 2) was based on the commonly used significance levels for two-sided chi-square tests. Given the higher prevalence of MSSA, two different levels of significance were chosen for MSSA (0.001) and MRSA (0.049). **Analysis of secondary endpoints** will involve adjustment for covariates such as age and gender using logistic regression modelling with GEE correction. However, the interpretation of local significances is not designed to be strictly confirmatory. Due to the multitude of secondary parameters and the lack of a hierarchical structure, a correction for multiple tests is not necessary. Descriptive analyses are performed following scaling and observed data distribution.

**Qualitative data** from focus groups will be transcribed and then analysed using qualitative content analysis [23]. Data collection will continue until thematic saturation is reached. The resulting category system will help to understand the feasibility of the intervention in daily practice from the perspective of providers in outpatient and hospital care. It will thereby provide additional information to the patient perspective evaluated via questionnaire data. Additionally, all qualitative data systematically collected or observed during the study will be considered as data. This means that not only information from focus groups and questionnaires will be analysed, but also all data documented during hotline calls or observed during site visits. This data will be collected by study personnel in the Heidenheim Clinic via a logbook. Entries of free text will be categorized thematically. Data entries will then be analysed descriptively following observed data distribution. Quantitative analysis will be carried out in Microsoft Excel (Version 2010) und IBM SPSS Statistics (Version 25). For qualitative data analysis MAXQDA (Version 2018) will be used.

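### Study staff document related adverse events only if they end study participation; those that end only decontamination rest on self-report, and reactions in patients who complete it have no designated route

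*Protocol article*

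**What the plan says.** The Adverse events section of the protocol article has two recording sentences and one expectation.

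- Recording by staff of the Heidenheim clinic: "All adverse events related to the intervention that lead to a discontinuation of the study will be documented by study personnel".
- Recording by patients: "Reasons for discontinuation of the decontamination procedure will be collected via patient questionnaires".
- Expectation, without a figure: "Adverse events directly related to the intervention (i.e. reaction of the skin, allergic reactions) are, however, expected to be rare".

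The Adherence to intervention section treats leaving the study and stopping the regimen as different events. It describes "discontinuation of the decontamination process (i.e. due to related side effects, lack of motivation) without wishing to be excluded from the study itself" and keeps such patients in the intention-to-treat analysis. On oversight it says: "A direct clinical supervision is not possible as the decontamination is self-administered in the home setting". Patients fill in a schedule on which they tick off completed steps.

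Table 3 lists patient questionnaires for acceptance, feasibility, satisfaction and compliance. It has no adverse-event endpoint. In Statistical analysis, the qualitative part says that "not only information from focus groups and questionnaires will be analysed, but also all data documented during hotline calls or observed during site visits". These entries go into a logbook and are grouped by theme. The Outcomes section says that the hotline information is collected anonymously.

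**The concern.** The staff rule makes recording depend on what follows the event. A patient with a reaction may leave the study, may stop decontamination and stay in, or may carry on to the end. Only the first is documented by staff. The protocol itself expects the second to occur, and nothing in the text rules out the third.

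This matters because the regimen is used at home without supervision, by people treated on the strength of a positive swab, and the Discussion looks ahead to adoption in routine care. Tolerability is part of what a payer or guideline group would ask about. Under the present rule, nearly all recorded events would be ones that ended something. The data could show neither how often reactions occur nor what share of them lead patients to stop. The expectation that events are rare could appear to be confirmed simply because most milder events were not counted.

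**Working it through.** The article gives no adverse-event rate, stopping rate or questionnaire return, so there is no figure of the plan to reproduce. The check is to follow each kind of related event through the stated routes.

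| What follows the event | Route in the article | Completeness |
|---|---|---|
| A: patient leaves the study | Documented by study personnel (Adverse events, first sentence) | Full, if the rule is followed |
| B: patient stops decontamination but stays in the study (foreseen in Adherence) | Reason given on patient questionnaire (Adverse events, second sentence) | Depends on return and on the patient naming the reaction |
| C: patient completes the regimen | None designated | Chance only |

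Let A, B and C be the numbers of events in each row, and r the share of B that is reported on a returned questionnaire, between 0 and 1.

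- All related events: A + B + C
- Events captured by the designated routes: A + rB
- Share captured: (A + rB) / (A + B + C)

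The share is highest at r = 1, where it equals 1 − C / (A + B + C). It reaches 1 only if no patient who completes the regimen has a reaction and every B event is reported. Otherwise the count is too low.

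**Illustration on assumed figures only.** Of 100 related events, let A = 10, B = 30 and C = 60.

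- Staff documentation alone: 10 / 100 = 10%.
- With the questionnaire at r = 0: (10 + 0) / 100 = 10%.
- With the questionnaire at r = 1: (10 + 30) / 100 = 40%.
- Outside both routes whatever r is: 60 / 100 = 60%.

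These figures show the mechanism and are not an estimate for this trial.

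**Other sources that might fill row C.**

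- The schedule, as described, records completed steps and not reactions.
- Questionnaires on satisfaction and feasibility may bring up complaints, but Table 3 does not assign them to adverse events.
- Hotline and site-visit entries depend on someone calling or noticing. The anonymous hotline entries cannot be tied to a treated patient or checked for duplicates.
- SSI surveillance covers both groups for 90 days after discharge, but it does not measure reactions to the wash, ointment or rinse.

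**The case against.** The strongest reply is that the article does not ignore patients who stop because of side effects. The questionnaire sentence stands directly after the staff rule, compliance is a listed questionnaire endpoint, and questionnaire data are entered in the eCRF. This stands. A reader might infer from the first sentence that these patients are lost by rule, and the document does not support that: they have a route, though a self-reported one.

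A reader might also infer that a planned harm rate is biased. None is planned. Table 3 has no adverse-event endpoint, and the article only states an expectation of rarity. The point is therefore about any count or tolerability statement that is later built on these records. Nor is it right that reactions in patients who complete the regimen could be noted nowhere: the logbook may pick some up, without being designated for it.

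It can further be said that the wording on discontinuing the study may be loose and meant to include stopping the regimen. On that reading staff would capture A + B, but C would still be missed. Finally, this is a condensed article, and the full protocol may say more about safety recording. That would excuse silence. Here, however, the article states which events are documented and attaches a condition to them, and it is this condition that needs changing or confirming.

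**Conclusion.** The point holds in this form: staff documentation of related adverse events is tied to leaving the study, events that end only decontamination depend on self-report, and related events in patients who complete the regimen have no designated route. A count from these sources is selected by outcome and too low. This assumes only that some reactions occur in patients who complete the regimen, or that some questionnaires are missing or silent on the reason.

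The size cannot be derived from the document. It is tempting to take half of the 13,260 patients, which is 6,630, and apply the 20 to 30% carriage from the Background: 6,630 × 0.20 = 1,326 and 6,630 × 0.30 = 1,989 treated at home. The text supports no such figure. Groups follow practice membership in the MRE-Network and no split is given in the text. Few gynaecology patients are expected to be decontaminated. Any reaction or leaving rate applied to these numbers would be invented.

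The primary endpoint and its analysis are not affected. The change is worth making because it improves the safety information at little cost.

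**What to change.** Reword the Adverse events section, and align the Adherence section with it, so that every adverse event related to decontamination is recorded whether or not the patient stops the regimen or leaves the study. State who records it.

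- Add a field for reactions to the existing decontamination schedule and a matching field in the eCRF. Have study staff check it with the patient at the admission visit, which every patient already has for the swab.
- Report the number of patients with at least one related event per patient who started decontamination, and whether the regimen was stopped. The denominator should include those who started on a PCR result, since the protocol lets decontamination begin on that basis.
- Keep the questionnaire reasons for stopping as a supplement. Do not use the anonymous hotline log for this rate.

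The cost is one extra form field, a short question at admission and some data-entry time. If the full protocol already records events in this way, the article's sentence should be corrected to match.

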### Outcomes

Colonization status (MRSA and MSSA) upon hospital admission will serve as the primary endpoint (see Table 3). Secondary endpoints include comparison of length of stay, recolonization and rehospitalisation as well as wound infection rates (SSI). In addition, associated costs of secondary care will be compared. Feasibility of decontamination measures and patient satisfaction with the intervention will be assessed via paper based questionnaires (patients) as well as focus groups (practice teams). In total we aim for 3–4 focus groups with 8–12 participants each. All focus groups will be recorded and subsequently transcribed. As clinical study staff is closely monitoring the implementation at primary care practices and is responsible for the overall project management, 1–2 focus groups with 4–6 participants will be conducted with this particular group. Feasibility of the intervention will also be assessed based on qualitative data (questions from providers and patients to the study coordination office) anonymously collected during the intervention period via the study hotline.

**Table 3 Tab3:** Primary and secondary endpoints, data sources und collection methods

Primary data collection			Routine data collection Heidenheim Clinic	Routine data collection Health insurance data
Patients	GPs, Link Nurses	Clinical data	Clinical data*	Routine data AOK-BW**
• Acceptance / feasibility / satisfaction (QS) • Compliance (QS)	• Acceptance/ feasibility / satisfaction (FG)	• Primary endpoint: Colonization upon hospital admission (MSSA und MRSA) (Lab) • Wound infection rates (SSI) • Recolonization with MRSA 3 + 6 months post-surgery (Lab) • Risk assessment	• MRSA colonization rates (2015–2018) • Length of stay • Rehospitalisation rates • Costs secondary care (incremental cost monitoring)	• MRSA colonization rates (2015 onwards) • Wound infection rates (SSI) • Rehospitalisation rates • Costs primary and secondary care (incremental cost monitoring)

*QS* Questionnaires, *FG* Focus groups, *Lab* Laboratory test result, (A) data for study group comparison (IG vs. CG) and time series analysis* (B) data for time series analysis only**

### Data collection and management

A pooled routine dataset is sent from the AOK Baden-Wuerttemberg (health insurance fund) as well as the Klinikum Heidenheim to the Institute for Clinical Epidemiology and Applied Biometry (IKEaB, University Hospital Tübingen). The IKEaB will deliver extracts of the pseudonymized patient dataset to the Insitute of Gerneral Medicine and Interprofessional Care (IAIV, University Hospital Tübingen) and the Steinbeis Business Academy for statistical analysis. Data access will be granted upon written requests of the evaluators (IAIV and Steinbeis Business Academy). All of these transfers will be carried out using a secure, encrypted protocol. The relevant data sources are subject to quality management processes. Primary data (i.e. questionnaire data as well as the lab results, wound findings) will be stored and entered manually by study personal of the Heidenheim clinic via an electronic Case Report Form (eCRF, Koordobas©) provided by the IKEaB. All paper-based data collection forms will be securely stored in the study centre of the Heidenheim clinic. Manually entered data will be subject to plausibility checks carried out by the IAIV. Audio transcripts from focus groups will be stored electronically in a secure folder at the IAIV. Only study personnel have access to this folder. There will be no paper based versions of the transcripts. After the end of the study, all paper and electronic documents will be stored for 10 years and subsequently deleted.

### Statistical analysis

**The primary endpoint** (comparison of colonization rates prior to surgery) will be analysed separately for MRSA and MSSA using logistic regression modelling with GEE (Generalized Estimation Equation) correction to account for potential cluster effects. The power calculation (see section 2) was based on the commonly used significance levels for two-sided chi-square tests. Given the higher prevalence of MSSA, two different levels of significance were chosen for MSSA (0.001) and MRSA (0.049). **Analysis of secondary endpoints** will involve adjustment for covariates such as age and gender using logistic regression modelling with GEE correction. However, the interpretation of local significances is not designed to be strictly confirmatory. Due to the multitude of secondary parameters and the lack of a hierarchical structure, a correction for multiple tests is not necessary. Descriptive analyses are performed following scaling and observed data distribution.

**Qualitative data** from focus groups will be transcribed and then analysed using qualitative content analysis [23]. Data collection will continue until thematic saturation is reached. The resulting category system will help to understand the feasibility of the intervention in daily practice from the perspective of providers in outpatient and hospital care. It will thereby provide additional information to the patient perspective evaluated via questionnaire data. Additionally, all qualitative data systematically collected or observed during the study will be considered as data. This means that not only information from focus groups and questionnaires will be analysed, but also all data documented during hotline calls or observed during site visits. This data will be collected by study personnel in the Heidenheim Clinic via a logbook. Entries of free text will be categorized thematically. Data entries will then be analysed descriptively following observed data distribution. Quantitative analysis will be carried out in Microsoft Excel (Version 2010) und IBM SPSS Statistics (Version 25). For qualitative data analysis MAXQDA (Version 2018) will be used.

**Subgroup analysis** is planned for patients from gynaecology as the criteria for initiating a decontamination procedure are mostly based on the recommendation of the supervising physician. Furthermore, the primary goal regarding this subgroup analysis is to extract prevalence rates – the success of the decontamination will most likely not be the main focus of the analysis. This is also linked to the small number of patients expected to undergo a decontamination procedure. All patients who are not undergoing a surgical procedure will be considered as a potential subgroup. This is due to the possibility of slight variation in the patient pathway as well as a different risk of complications upon follow-up. All other stratifications will be considered in the statistical model. The robustness of primary and secondary findings will be assessed through sensitivity analysis. Depending on the proportion of missing values, we will either use imputation or only complete data-sets.

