### Study design

In order to achieve these objectives the study will employ a controlled study design (A) with a time series analysis (pre-post comparison) on clinic and district level (B) (Fig. 1, Table 2). There is no randomization on practice or patient level. A detailed overview of the endpoints for analysis (A) and (B) can be found in under ‘Outcomes’.

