### Recruitment

Patients will be allocated to either study group based on their GPs. GP practices will be predefined as either control or intervention practice based on their participation in the regional MRE-Network. The intervention group will only contain practices that partake in the MRE-Network Heidenheim, while the control group will include non-participating practices from Heidenheim as well as other districts. With the engagement of the physicians association Heidenheim (Kreisärzteschaft Heidenheim) in the conception of the project, we expect a high acceptance amongst GPs. The recruitment of practices is jointly carried out by the Association of Statutory Health Insurance Physicians Baden-Wuerttemberg (Kassenärztliche Vereinigung Baden-Württemberg) and the physician association Heidenheim.

The intervention phase will stretch over a period of 24 months and is preceded by a 6 months recruitment and preparation phase (also see Fig. 2).

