#### Patient pathway

##### (1) **Study inclusion and risk assessment** (intervention and control group)

All patients, irrespective of risk of S Aureus colonization will be screened for risk of colonization with MRSA according to criteria defined by the Robert-Koch Institute (RKI) in the medical consultation session roughly 5 weeks prior to hospital admission (also see Fig. 4).

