There is a risk of selection bias due to the recruitment of intervention practices via the MRE-Network Heidenheim. Additionally, the local community hospital has been active in MRE-prevention prior to the intervention onset. In order to identify potential (positive) effects of prior efforts, we carry out a time series analysis on a hospital and district level. The successful implementation of patient pathways within the hospital setting has proven to be partly dependent on departmental particularities (i.e. staffing, leadership). Current efforts are made to homogenize processes across all relevant departments. Assessing the feasibility of the novel care pathway in the clinical and outpatient setting will therefore take a central role in the overall evaluation.

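### The primary comparison of practice groups formed by MRE-Network membership has a stated cluster correction but no stated adjustment for baseline differences

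*Protocol article*

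**What the plan says.** **Allocation.** Study design states: "There is no randomization on practice or patient level". Recruitment states: "GP practices will be predefined as either control or intervention practice based on their participation in the regional MRE-Network". Intervention practices are members of the Heidenheim network only, "while the control group will include non-participating practices from Heidenheim as well as other districts". The Discussion acknowledges that recruiting intervention practices through the network risks selection bias.

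**Primary model.** Under Statistical analysis, the comparison of colonisation at admission "will be analysed separately for MRSA and MSSA using logistic regression modelling with GEE (Generalized Estimation Equation) correction to account for potential cluster effects". Two-sided levels are 0.001 for MSSA and 0.049 for MRSA.

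**Secondary models.** In the same paragraph, the analysis of secondary endpoints "will involve adjustment for covariates such as age and gender using logistic regression modelling with GEE correction".

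**Other relevant text.** The subgroup paragraph says that other stratifications will be considered in the model, without naming any, and promises sensitivity analyses for primary and secondary findings. Patient pathway step 1, which covers both arms, says: "All patients, irrespective of risk of S Aureus colonization will be screened for risk of colonization with MRSA according to criteria defined by" the RKI, about five weeks before admission. Table 3 lists this risk assessment among the collected clinical data. After mentioning selection bias and then the hospital's earlier MRE-prevention work, the Discussion says: "In order to identify potential (positive) effects of prior efforts, we carry out a time series analysis on a hospital and district level".

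**The concern.** Arm membership is fixed by a practice characteristic that existed before the study and is related to the outcome. The article's section on existing MRE-prevention activities lists screening of at-risk patients, decontamination, and education of patients and providers as network activities. Control patients may also come from other districts. Carriage before any study decontamination could therefore differ between the arms, in either direction.

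A logistic GEE with arm as its only regressor estimates the intervention effect plus that baseline difference. Allowing for correlation within practices widens the confidence interval around this sum but does not separate the two parts. A larger sample does not help either: with 13,260 patients a modest baseline gap is enough to give a significant result.

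What is at stake is the study's only confirmatory result. As the text stands, the exploratory secondary endpoints have a stated adjustment and the confirmatory one has none, although a relevant baseline variable is recorded in both arms.

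**Working it through.** **The plan's own figures.** The two levels add up: 0.001 + 0.049 = 0.05. The 92% power cannot be reproduced, because the assumed rates and the allocation ratio are not in the text (Fig. 3 is not shown). For scale, with 1:1 allocation and no clustering, 92% power corresponds to these reductions:

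- MSSA at 0.001: 20% to 16.8%, 25% to 21.6%, or 30% to 26.3%.
- MRSA at 0.049: 1.0% to 0.50%, 1.5% to 0.87%, or 2.0% to 1.26%.

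The starting rates are assumptions taken from the Background, which gives 20 to 30% for *S. aureus* and 1 to 2% for MRSA.

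**Question.** If the intervention does nothing but the arms differ at baseline, how often does the unadjusted test reject?

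**Inputs.** N = 13,260 and the two levels come from the protocol. Allocation of 1:1 (n = 6,630 per arm) and all baseline gaps are assumed. A design effect of 2 is an assumed sensitivity value, entered as n = 3,315.

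**Formula.** With d = p1 − p2 and p̄ = (p1 + p2)/2:

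- s0 = √[2p̄(1−p̄)/n]
- s1 = √[p1(1−p1)/n + p2(1−p2)/n]
- rejection probability = Φ((d − z·s0)/s1) + Φ((−d − z·s0)/s1)
- z = 3.2905 for 0.001 and 1.9686 for 0.049

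The second term is negligible below.

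**MSSA, 25% vs 23%.** s0 = 0.007418, s1 = 0.007416. (0.02 − 3.2905 × 0.007418)/0.007416 = −0.594, and Φ = 0.276.

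**MSSA, 25% vs 22%.** s0 = 0.007364, s1 = 0.007360. (0.03 − 3.2905 × 0.007364)/0.007360 = 0.784, and Φ = 0.783.

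**MRSA through a risk-factor imbalance.** Assume MRSA carriage of 3% with an RKI risk factor and 0.4% without.

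- 45% of controls and 30% of intervention patients with a risk factor: 0.45 × 3% + 0.55 × 0.4% = 1.57%, and 0.30 × 3% + 0.70 × 0.4% = 1.18%. Apparent risk ratio 1.18/1.57 = 0.75. s0 = 0.002023, s1 = 0.002022. (0.0039 − 1.9686 × 0.002023)/0.002022 = −0.040, and Φ = 0.484.
- Milder split, 40% vs 35%: 0.40 × 3% + 0.60 × 0.4% = 1.44%, and 0.35 × 3% + 0.65 × 0.4% = 1.31%. Rejection probability 0.097.

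| Assumed baseline gap, no true effect | Level | Rejects, no clustering | Rejects, design effect 2 |
|---|---|---|---|
| MSSA 25% vs 23% | 0.001 | 28% | 8% |
| MSSA 25% vs 22% | 0.001 | 78% | 34% |
| MRSA 1.57% vs 1.18% | 0.049 | 48% | 27% |
| MRSA 1.44% vs 1.31% | 0.049 | 10% | 7% |

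In the design-effect column the test uses the correct, wider standard error, as a GEE would. Rejection falls but stays above the nominal level in every row, because the quantity being estimated is still biased.

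**Can the time series reveal a gap between the arms?** Table 2 has one row for the clinic and one per district. Heidenheim control practices and intervention practices fall into the same clinic and district series. The routine sources in Table 3 list colonisation rates for MRSA only, so there is no historic MSSA series. As laid out, it cannot show whether the two practice groups differed beforehand.

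**The case against.** **The article does not call the primary model unadjusted.** Logistic GEE admits covariates, the subgroup paragraph mentions stratifications and sensitivity analyses, and an analysis plan not shown here may list confounders. That is a fair caution: the documents do not establish that the final analysis will be unadjusted, or that the risk assessment will go unused. But the article does more than stay silent. It describes both sets of models in one paragraph and gives covariate adjustment to the secondary set only, and the stratification sentence commits the primary model to no confounder. Followed as written, the primary estimate is unadjusted.

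**The time series.** A reader might infer that the authors offer it as their cure for practice selection. The text does not support this. It ties the series to the effects of prior efforts, directly after mentioning the hospital's earlier prevention work, and never says that it corrects practice selection. What stands is narrower: the series as laid out should not be relied on for that purpose. A footnote to Table 3 allows clinic routine data for comparing the arms, but no pre-period split by practice group is described.

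**The mechanism is weaker for MSSA.** Network activity concerns multidrug-resistant pathogens, and the Background says that routine preoperative measures target MRSA only. The network argument therefore supports a baseline gap in MRSA more than in MSSA. Nearly every district in the state has a network, so controls from other districts may be exposed too and the direction of any bias is open. For MSSA, the case rests on general non-comparability of the practice groups.

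**The magnitudes are chosen.** This stands. The baseline gaps, the risk-factor split and 1:1 allocation are assumptions, and the milder MRSA split takes 48% down to 10%.

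**Conclusion.** The concern holds in this form: a non-randomised comparison with an acknowledged risk of selection bias has a primary model whose only stated correction is for clustering, while covariate adjustment is stated for the secondary endpoints. Under the assumptions shown, false rejection runs from 8% to 78% for MSSA against a nominal 0.1%, and from 7% to 48% for MRSA against a nominal 4.9%. These figures show what plausible gaps would do; they do not estimate the actual bias. Confidence is high that the text leaves the primary estimate open to confounding, and lower on its size and direction, especially for MSSA.

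**What to change.** 1. Prespecify adjustment for age, sex and the RKI risk assessment in both primary GEE models, plus hospital department if it is recorded. The RKI criteria concern MRSA, so they will probably explain less in the MSSA model. Report the unadjusted model as a sensitivity analysis.
2. Add a sensitivity analysis that restricts controls to Heidenheim practices.
3. As a baseline diagnostic only, compare the intervention arm's GP cultures taken before decontamination with the control arm's admission cultures, using the same covariates. Both sample nares, throat and any wounds. The GP cultures are taken about two weeks before surgery and read in the Tübingen laboratory, whereas the laboratory for admission cultures is not stated. A difference may therefore reflect timing or laboratory as well as selection, and should not be reported as an estimate of bias.
4. State that the hospital and district series, being unsplit by practice group and without historic MSSA colonisation data, is not relied on to address practice selection. There is no explicit claim to delete.

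The cost is analysis-plan wording and a few model runs, with no new clinical procedure. It should be confirmed that age, sex, department and practice district are in the study database, since the article does not list them as collected items. Event numbers should bear a short covariate list: even at 1.0% vs 0.5% MRSA, 6,630 × 0.010 + 6,630 × 0.005 ≈ 99 events.
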